### Strategies to improve adherence to interventions {11c}

Automatic SMS reminders will be introduced. Every week, the patient will receive a message with specific individualized dosing information. The reminder of the IMP will be returned to the examiner.

### Relevant concomitant care permitted or prohibited during the trial {11d}

Participants should record and report the number of days spent actively sunbathing, if at least half of the body is exposed to the sun.

#### Concomitant medication permitted during clinical trials

With the exception of medication that is expressly prohibited, all medication is allowed without restriction.

#### Prohibited concomitant medication during the clinical trial

Systemic immunosuppressive pharmacotherapy (including corticotherapy) more than 14 days in duration or exceeding the length of hospitalization (if the actual duration of treatment could not be determined), or local corticotherapy applied at the site of wound healing more than 5 days duration.Systemic pharmacotherapy with digitalis cardioactive glycosides at any dosage if not possible to ensure regular monitoring of calcium with a minimum measurement interval of once per week, always before the administration of IMP.Systemic pharmacotherapy with hydrochlorothiazide at a dose higher than 12.5 mg/day if not possible to ensure regular monitoring of calcium with a minimum measurement interval once per week, always before the administration of IMP.Chronic treatment with teriparatide.Chronic treatment with bile acid sequestrant.Chronic treatment with vitamin D or its derivatives (alphacalcifediol, calcitriol, paricalcitol) including ergocalciferol (vitamin D2) in addition to IMP.Administration of any medicinal products or food supplements containing any calcium salt in any dosage if not possible to ensure regular monitoring of calcium with a minimum measurement interval of once every 2 months, always before the administration IMP.

### Provisions for post-trial care {30}

There are no provisions included. Entering the trial is voluntary. The trial is not sponsored by any pharmaceutical company. The trail will be paid from public funds provided for Na Homolce Hospital. Therefore, it is not dependent on the pharmaceutical industry, but is conceived as low-cost. Therefore, there is no financial reward for participation in the trial, nor is there any other compensation for the subject in connection with participation in the trial (e.g., reimbursement of travel expenses).

### Outcomes {12}

#### Efficacy outcomes

##### Primary endpoint

The number of all postoperative sternotomy healing complications in two parallel patient groups with cholecalciferol or placebo treatment (calculated incidence in %).Patients with sternotomy healing complication have to fulfill the following 2 conditions that can occur at any time during the clinical trial period (evaluation time points: 6 weeks and 6 months following sternotomy):
Sternotomy soft tissue dehiscence (evaluated by medical examination) by visual inspection, palpation, and auscultation in the surgical area of sternotomy.Sternal bone crepitation (evaluated by medical examination) by visual inspection, palpation, and auscultation in the surgical area of sternotomy.Patients not fulfilling both conditions will be considered without sternotomy healing complications.

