#### Sternotomy healing and its complications

Complication rates for median sternotomy range from 0.5 to 5%; however, mortality rates from complications are variable (7–80%). Complications may affect the presternal (cellulitis, sinus tracts, abscess), sternal (osteomyelitis, dehiscence), or retrosternal (mediastinitis, hematoma, abscess) compartments [15]. According to previous studies, superficial complications occurred in 1.1–6.7% of patients, whereas the incidence of deep sternal wound complications ranged from 0.1 to 3.7% [16–18]. In another single-center study with 1279 patients, 76 patients (5.8%) developed sternal wound complications, superficial healing disorders occurred in 43 patients (3.3%), while 33 patients (2.5%) developed deep wound complications [19].

For the purposes of this clinical trial, sternotomy healing complications within the trial are defined as follows:
Presternal complications—an infective or non-infective complication affecting the superficial soft tissues occurring at any time during the clinical trial, not affecting the sternum or mediastinum.Sternal complications—an infective or non-infective complication affecting the sternum (resulting in partial or complete sternal dehiscence or instability), occurring at any time during the clinical trial.Retrosternal complications—an infective or non-infective complication affecting the mediastinal tissues occurring at any time during the clinical trial.

The optimal length of the sternum healing is, per se, the subject of debate. According to one study published in 2014, the sternum is not fully recovered after 3 nor after 6 months [20]. In this clinical trial, a 6-month period for evaluation was selected due to the high probability of capturing any sternotomy healing complications related to bones and soft tissues during the trial.

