### Objectives {7}

The primary objective of this clinical trial is to compare the incidence of all postoperative sternotomy healing complications (presternal, sternal, and retrosternal) in two parallel patient groups with cholecalciferol or placebo treatment.

As a primary hypothesis, it has been expected that cholecalciferol supplementation in heart surgery patients with deficient or insufficient blood calcidiol concentration (based on initial calcidiol blood concentration) will show a reduced incidence of postoperative sternotomy healing complications within the 6-month period after sternotomy.

The secondary objectives are focused on general patient recovery: sternal bone healing grade at the end of the trial, length of hospitalization, number of days spent in the ICU, number of days spent on mechanical ventilation, and number of hospital readmissions for sternotomy complications.

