### Methods for additional analyses (e.g., subgroup analyses) {20b}

Additional subgroup analyses are planned of the primary endpoint in groups with different initial calcidiol concentrations. Three subgroups will be evaluated: 1st with initial calcidiol concentration ≤ 25 nmol/L, 2nd with initial calcidiol concentration > 25 nmol/L and ≤ 50 nmol/L, and 3rd with initial calcidiol concentration > 50 nmol/L. The chi-square test will be used for this analysis.

Another subgroup analysis of the primary endpoint will be focused on sternotomy complication type: presternal, sternal, and retrosternal.

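### The primary endpoint has no mediastinal criterion, so a retrosternal complication without both external wound signs is scored as a non-event although the objective counts it

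*Protocol article*

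**What the plan says.** All references are to the protocol article.

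- **Objectives {7}:** the aim is to "compare the incidence of all postoperative sternotomy healing complications (presternal, sternal, and retrosternal"), in the two treatment groups.
- **Sternotomy healing and its complications:** the third trial-specific definition reads "Retrosternal complications—an infective or non-infective complication affecting the mediastinal tissues occurring at any time during the clinical trial". The same section names mediastinitis, hematoma and abscess as examples for that compartment.
- **Outcomes {12}, Primary endpoint:** "Patients with sternotomy healing complication have to fulfill the following 2 conditions". The first is "Sternotomy soft tissue dehiscence (evaluated by medical examination) by visual inspection, palpation, and auscultation in the surgical area of sternotomy". The second is "Sternal bone crepitation (evaluated by medical examination) by visual inspection, palpation, and auscultation in the surgical area of sternotomy". Both signs are thus sought in one way only, "by visual inspection, palpation, and auscultation in the surgical area of sternotomy". A closing sentence classes anyone who does not meet both as having no complication.
- **Methods for additional analyses {20b}:** "Another subgroup analysis of the primary endpoint will be focused on sternotomy complication type: presternal, sternal, and retrosternal".
- **Secondary endpoints and Table 3:** the chest CT at month 6 serves the bone healing grade. Readmissions for sternotomy complications are a separate secondary endpoint.
- **Assessments and visits:** the daily in-hospital check is also an examination of the sternotomy.

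**The concern.** The objective and the endpoint do not describe the same event. Three sections treat a complication of the mediastinal tissues as an event in its own right. The endpoint rule recognises two signs, one in the soft tissue and one in the bone, and excludes everything else. A mediastinal hematoma or abscess beneath a closed, stable sternum meets the trial's own definition but is tabulated as no complication.

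Three things are at stake:

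- The reported incidence would not be the incidence of all complications that the objective promises.
- The planned split by type has no stated basis for its retrosternal category, because a counted event carries no information that would place it there.
- If the 5% and 1% behind the sample size cover all sternotomy complications, fewer events will be scored than were planned for.

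**Working it through.** **1. Definition against endpoint rule**

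| Retrosternal complication presents with | Under the trial definition | Under the endpoint rule as written | If either sign alone sufficed |
|---|---|---|---|
| Neither dehiscence nor crepitation | event | non-event | non-event |
| One of the two signs | event | non-event | event, type not identified |
| Both signs | event | event, type not identified | event, type not identified |

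The first row is the core of the point. Relaxing the both-signs requirement does not rescue it, because the rule has no criterion for the mediastinum. The converse also holds: adding a source of evidence, such as imaging, without changing the both-signs requirement would leave the first two rows as non-events. Both parts of the rule have to change.

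**2. Other sources.** The month-6 CT, readmissions, daily surgical examination, serious adverse events and the physician questionnaire all exist in the plan. None is stated to contribute to the primary endpoint.

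**3. The plan's sample size.** The Sample size {14} section gives p1 = 0.05, p2 = 0.01, α = 0.05, β = 0.2 and 284 per arm. With p̄ = (p1 + p2)/2 = 0.03, pooled variance under the null and no continuity correction:

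n = [z_α·√(2p̄(1−p̄)) + z_β·√(p1(1−p1) + p2(1−p2))]² / (p1−p2)²

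Two-sided: (1.960 × 0.24125 + 0.8416 × 0.23958)² / 0.04² = 284.3. This reproduces 284. One-sided, the same formula gives 224. The plan's figure is thus the two-sided one despite its one-sided label. That is a separate matter, but it is why two-sided power is used below.

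**4. Illustration of size.** Assumption: a share m of events is retrosternal and missed, equally in both arms, so the rates become 0.05(1−m) and 0.01(1−m). The documents do not give m. The only nearby figure is the cited single-center series, with 33 deep complications among 76, and 33/76 = 43%. Deep is not the same as retrosternal, so 43% is an upper bound for that series only.

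Power = Φ{[(p1−p2)√n − 1.960·√(2p̄(1−p̄))] / √(p1(1−p1) + p2(1−p2))}

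At n = 300 and m = 0: (0.6928 − 0.4728)/0.2396 = 0.918, so power is 82%. At m = 43%: (0.3949 − 0.3593)/0.1826 = 0.195, so power is 58%.

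| m | Rates (%) | Power, 284 per arm | Power, 300 per arm |
|---|---|---|---|
| 0 | 5.0 v 1.0 | 80% | 82% |
| 10% | 4.5 v 0.9 | 76% | 78% |
| 20% | 4.0 v 0.8 | 70% | 73% |
| 30% | 3.5 v 0.7 | 64% | 67% |
| 43% | 2.85 v 0.57 | 55% | 58% |

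**The case against.** **The both-signs rule is at least as much to blame as the examination method.** This stands. The rule also scores a purely presternal event as none, since by definition such an event spares the sternum, and a sternal event without soft tissue dehiscence. A reader might infer that the choice of a physical examination is the whole cause; the text does not support that. What remains is that repairing the both-signs rule alone would still leave isolated retrosternal events unscored.

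**Not every retrosternal complication is lost.** This also stands. One accompanied by both signs counts. A reader might infer that all are scored as none, or that the retrosternal category will be nearly empty, but the documents do not say how often both signs accompany such an event.

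**The trial does look elsewhere.** The Discussion even describes the trial CT as an examination of the mediastinum, and there are readmission, adverse event and questionnaire data. So it would be wrong to say the trial collects nothing on the mediastinum. The narrower statement survives: nothing of this is said to reach the primary endpoint.

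**The severity and the power loss are not established.** It is tempting to call retrosternal events the most severe class, but the article gives one mortality range for sternotomy complications together and does not rank the compartments. It is also tempting to treat the 5% as including events the endpoint cannot see. That figure comes from unpublished internal data whose method of ascertainment is not described. In addition, the both-signs rule already reduces the countable events, so the loss due to retrosternal events alone cannot be isolated.

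**Conclusion.** The point holds as a conflict within the protocol article. The objective, the definitions and the split by type include retrosternal complications, while the endpoint rule has no criterion for them and explicitly classes patients without both external signs as complication-free. This is not detail left to another document, because the rule is stated as complete.

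The conclusion rests on the wording alone and does not depend on the power figures. Those rest on an assumed retrosternal share, equal loss in both arms, and 5% and 1% being rates of all complications that are otherwise fully captured. They show that the effect on power could range from small to substantial, and no value within that range can be singled out from the documents.

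**What to change.** Reconcile the definitions, the objective, the primary endpoint and the analysis by type.

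1. Under Primary endpoint, add a retrosternal criterion: a complication meeting the trial's own definition ("an infective or non-infective complication affecting the mediastinal tissues occurring at any time during the clinical trial"), documented in hospital records by operative finding, clinically indicated imaging, microbiology or discharge diagnosis, and classified blind to arm.
2. State that this criterion alone makes the patient an event.
3. Amend the sentence that classes everyone not meeting both conditions as complication-free. Without steps 2 and 3 the score would not change.
4. Use the same source to assign the retrosternal category in the analysis by type.

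If this is not wanted, remove retrosternal from the objective and from the analysis by type, and restrict the trial's conclusion to match.

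**Cost.** No new patient procedure is needed, and the trial already draws on hospital records for secondary endpoints. The change is nevertheless an amendment to the primary endpoint of an ongoing trial, to be communicated to the ethics committee and the regulator. It requires record abstraction, including for patients already enrolled, and the added events will depend on what routine care documented.

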### Sample size {14}

To determine the optimal trial patient population, a sample size calculation was made. This calculation is based on the estimated incidence of sternotomy healing complications, which is typically around 5% at our cardiac surgery center (unpublished internal data). This is in agreement with data published previously. If we assume the same incidence during the trial, and considering vitamin D supplementation, we expect an incidence of roughly 1%. Thus, 284 patients are needed in the placebo arm and 284 patients in the treated arm, considering a one-sided statistical alternative. We plan to enroll approximately 300 patients in each arm, altogether 600 patients.

MedCalc software (version 17.8.6) was used to calculate sample size. The following input data was used for sample size calculation:
*p*1 = 0.05, incidence of event occurrence (sternotomy complications) in the placebo arm*p*2 = 0.01, incidence of event occurrence (sternotomy complications) in the treatment arm (cholecalciferol)α = 0.05, probability of type I errorβ = 0.2, probability of type II error

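### The primary endpoint requires soft-tissue dehiscence and sternal crepitation together, which contradicts the objective of counting complications in every compartment and leaves the 5% planning rate without a matching case definition

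*Protocol article*

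**What the plan says.** Objectives {7} sets out to "compare the incidence of all postoperative sternotomy healing complications (presternal, sternal, and retrosternal"), and the first line under Primary endpoint in Outcomes {12} likewise speaks of all such complications.

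The introduction, under Sternotomy healing and its complications, defines three types for this trial. A presternal complication is "an infective or non-infective complication affecting the superficial soft tissues occurring at any time during the clinical trial, not affecting the sternum or mediastinum". Sternal and retrosternal complications are those affecting the sternum and the mediastinal tissues respectively. Each may be infective or not.

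The operational rule under Primary endpoint is narrower: "Patients with sternotomy healing complication have to fulfill the following 2 conditions that can occur at any time during the clinical trial period". The first condition is dehiscence of the soft tissue over the sternotomy. The second is "Sternal bone crepitation (evaluated by medical examination"). The rule closes with "Patients not fulfilling both conditions will be considered without sternotomy healing complications".

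Methods for additional analyses {20b} adds: "Another subgroup analysis of the primary endpoint will be focused on sternotomy complication type: presternal, sternal, and retrosternal".

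Sample size {14} takes a placebo incidence "which is typically around 5% at our cardiac surgery center (unpublished internal data"), says that this agrees with published data, and assumes 1% on cholecalciferol. It arrives at 284 per arm, with about 300 per arm planned.

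**The concern.** The rule that decides who has a primary event does not measure the objective. An analyst who follows it would record a patient with a documented superficial wound complication as complication-free. The same happens to a patient with an unstable sternum under intact skin, or with mediastinitis that does not show both signs.

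Two things are at stake. The first is what the trial estimates: an overlap of two clinical signs rather than the incidence of healing complications. The second is the number of events. If the planning rate counts all complications and the endpoint counts a subset, fewer events will occur than the sample size assumes.

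**Working it through.** **1. The definitions side by side**

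| Type of complication | Defined as a complication? | Counted by the two-sign rule? |
|---|---|---|
| Isolated presternal (sternum spared) | Yes | No: a spared sternum gives no crepitation |
| Sternal instability under intact soft tissue | Yes | No: no soft-tissue dehiscence |
| Retrosternal without both signs | Yes | No |
| Any complication with both signs | Yes | Yes |

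The definition of presternal ends with "occurring at any time during the clinical trial, not affecting the sternum or mediastinum", so the conflict with a required sternal sign is one of definition and needs no numbers. In the analysis by type, isolated presternal events are absent by construction.

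**2. The plan's own sample size**

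Inputs from Sample size {14}: p1 = 0.05, p2 = 0.01, α = 0.05, power 0.80. The mean rate is p̄ = 0.03.

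n per arm = [z_α·√(2p̄(1−p̄)) + z_β·√(p1(1−p1) + p2(1−p2))]² / (p1−p2)²

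- Two-sided: [1.960 × √0.0582 + 0.842 × √0.0574]² / 0.0016 = 284.3. This reproduces the stated 284.
- One-sided, as the text says: the same formula with 1.645 gives 223.8, or 224. This does not reproduce 284.

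Because the text says one-sided and the figure is two-sided, both are shown below.

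**3. What the 5% probably counts**

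The nearest published figure in the introduction is the single-center series with 76 complications (5.8%): 43 superficial (3.3%) and 33 deep (2.5%). The superficial share is 43/76 = 57% and the deep share 33/76 = 43%. The 5% is close to the combined figure, not to the deep one. This is an inference, because the protocol does not define the cases behind its internal 5%.

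**4. Illustrative power at 300 per arm**

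No two-sign rate is given, so the control rate is an assumption. The planned relative reduction is kept (1 − 0.01/0.05 = 80%, so p2 = p1/5). Power is the sum of the binomial probabilities of all outcome pairs for which the Pearson chi-square test without continuity correction rejects at 0.05. The one-sided column uses the critical value 1.645 in the direction of benefit.

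| Control rate | Source of the rate | Active rate | Expected events, placebo vs active | Power, two-sided | Power, one-sided |
|---|---|---|---|---|---|
| 5% | Planning rate | 1% | 15 vs 3 | 86% | 92% |
| 3.7% | Top of the cited range for deep complications | 0.74% | 11.1 vs 2.2 | 74% | 83% |
| 2.5% | Deep rate in the cited series | 0.5% | 7.5 vs 1.5 | 54% | 68% |
| 2.2% | 5% × 33/76 = 2.17% | 0.43% | 6.5 vs 1.3 | 47% | 62% |
| 1% | Assumed, within the cited deep range of 0.1–3.7% | 0.2% | 3 vs 0.6 | 20% | 35% |

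The first row exceeds 80% for two reasons: 300 per arm is more than 284, and exact power here is higher than the normal approximation, which gives 82% at 300 per arm (two-sided).

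**The case against.** **A drafting slip.** The closing sentence may have been meant to exclude only patients with neither sign. If so, one corrected sentence removes most of the problem and the power question with it. But the rule first says that the conditions have to be fulfilled and then excludes anyone without both, so the text as it stands is an AND rule. What stands of the objection is that the sponsor's intent should be established when the sections are reconciled.

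**The 5% may already be a two-sign rate.** It is unpublished internal data with no case definition, so the center could have counted by its own rule. This stands. A reader might infer that the 5% does not apply and that 80% power cannot be reached. The documents do not support that. They give no two-sign rate, and with the one-sided alternative that the text declares, power is still 83% at a 3.7% control rate.

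**2.2% is not a ceiling.** A reader might take 33/76 of 5% as the most that can remain. It applies one series' split to another center's rate. That series' own deep rate is 2.5%, and the protocol cites deep rates up to 3.7%. In the other direction, the two-sign event may be rarer than all deep complications, since deep cases lacking either sign are dropped as well.

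**Presternal events are not excluded in every patient.** The signs may occur at any time during the trial, so a patient with a presternal event and a separate sternal event could qualify. Only isolated presternal complications are shut out.

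**Timing.** A reader might infer that in-hospital events are lost because only 6 weeks and 6 months are named as evaluation points. The text does not clearly say so. The conditions may occur at any time, and Assessments and visits provides daily in-hospital examinations for the outcome measures.

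**Conclusion.** The contradiction holds on the protocol's own text. The two-sign rule conflicts with the objective, with the endpoint's own opening line, with the definition of a presternal complication and with the planned analysis by type. It is a stated rule, not a detail left to a fuller document, and it decides who counts as a primary event, so it must be resolved.

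The effect on power is plausible but not established. It rests on three assumptions: that the 5% counts all complications, that the two-sign rate resembles the cited deep rates, and that the 80% relative reduction carries over. Under these, two-sided power at 300 per arm runs from 74% at a 3.7% control rate down to 20% at 1% (one-sided 83% to 35%), against 86% (92%) at the planning rate.

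**What to change.** Before unblinding, reconcile the Primary endpoint text with the definitions in the introduction, Objectives {7}, Sample size {14} and the by-type analysis in {20b}. Replace the both-conditions rule with: a patient has the primary event if any presternal, sternal or retrosternal complication, as defined in the introduction, occurs during the trial, counted once per patient. Report the two-sign event as a secondary outcome. State which cases the internal 5% counts, so that it can be matched to the endpoint. If it is the all-complication rate, the planned 5% versus 1% comparison at 300 per arm stands.

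If the two-sign rule is truly intended, keep it, but restate the objective, the event rates and the power for that event, and revise the analysis by type.

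The cost is a protocol amendment while the trial is recruiting. Milder complications will enter the endpoint, as the objective already implies. It must also be confirmed that the component findings, retrosternal ones included, can be retrieved from the wound examinations and hospital records. The protocol schedules the examinations but does not say that each component is recorded at every one.
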